### Plans to promote participant retention and complete follow-up {18b}

This study is funded by a $20,000 grant from the Central Surgical Association. The grant will be used to reimburse participants’ transportation costs with a $25 gift card for completed 1-yearfollow-up and a $75 gift card for completed 2-yearfollow-up.

### Data management {19}

Patient characteristics and operative details will be captured in the ACHQC database, accessed using an assigned username and password. Treatment arm allocation, postoperative complications, CT results, and patient-reported quality of life scores will be collected in REDCap®, a secure electronic database accessed by the investigator and designated study team members using an assigned login and password. Only the principal investigator, research coordinators, and biostatisticians will have access to patient data for routine data quality assessments and data analyses. All electronic records pertaining to the clinical study will be password-protected, and only approved study members listed on the Cleveland Clinic Foundation Institutional Review Board (IRB) protocol will have password access.

### Confidentiality {27}

Anonymity and confidentiality of subjects participating in this study will be maintained. Every effort will be made to maintain the confidentiality of documents that identify the subject by name (e.g., signed informed consents or clinic charts), except when necessary to allow monitoring by the Office of Research Compliance at the Cleveland Clinic or other regulatory authorities.

### Plans for collection, laboratory evaluation, and storage of biological specimens for genetic or molecular analysis in this trial/future use {33}

Not applicable, we will not obtain biological specimens for genetic or molecular analysis.

## Statistical methods

### Statistical methods for primary and secondary outcomes {20a}

Analyses will be done under the normality assumption, if appropriate. Patient characteristics will be summarized overall and by randomized group, and differences will be described as standardized effects. All analyses, using the intent-to-treat population, will be performed with SAS and R software (version 9.4, Cary, NC; version 4.0.0, Vienna, Austria, respectively). Tests will be considered significant at a 5% level.

The primary study endpoint is 2-year composite hernia recurrence rate as a binary outcome (yes or no). Unadjusted and adjusted logistic regression will compare recurrence rates between the two repair techniques at 2 years. The adjusted model will include pre-specified covariates related to baseline disease severity: patient BMI, recurrent parastomal hernia, stoma disposition (stoma re-matured at a new site versus not), and type of stoma. Results, obtained using g-computation, will be presented as relative and absolute risk differences with a 95% confidence interval. Unbalanced follow-up times will be accounted for by using rate ratio and rate difference. As a sensitivity analysis, we will assess the treatment effect on time to hernia recurrence using a Cox proportional hazard model. Results will be presented by hazard ratio and 95% confidence interval, while adjusting for the pre-specified covariates.

The secondary endpoints are not dependent on the primary endpoint. The secondary endpoints are hospital length-of-stay, readmission, wound morbidity (SSI, SSO, or SSOPI), re-operation (stoma necrosis, mesh-related complication, mucocutaneous stoma disruption, and hernia recurrence requiring reoperation), and patient-reported outcomes, including PROMIS scores, HerQLes scores, opioid consumption at 30 days, stoma-relatedquality-of-life, and decision regret scores. Comparisons of categorical endpoints will be performed using chi-squared tests or Fisher’s exact test. Comparisons of continuous endpoints will be performed using two-sample*t*-tests or Wilcoxon rank-sum tests.

Additional analysis, such as mediation analysis, will be performed if the Data Safety and Monitoring Board (DSMB) or the investigators suspect potential dependent endpoints (for example, SSI and 2-year recurrence).

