### Sample size {14}

Based on the post hoc analysis of a large RCT, we predict that the retromuscular Sugarbaker technique will be superior to the keyhole mesh approach and reduce 2-year parastomal hernia recurrence by 20%. With an *α* of 0.05 and power of 80%, we calculated a necessary sample size of 118 patients—59 in each arm to demonstrate this 20% absolute reduction in 2-year parastomal hernia recurrence. Assuming a 20% rate of patients lost to follow-up, an enrollment goal of 142 patients was defined.

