## Data collection and management

### Plans for assessment and collection of outcomes {18a}

Patient characteristics and operative details will be captured in the ACHQC database, per our practice standard. Patient-reported quality of life at baseline will be collected with the standard ACHQC questionnaire, which includes the short-form PROMIS Pain Intensity Scale [14] and HerQLes, validated for assessing quality-of-life related to abdominal wall function [15]. Preoperative stoma-related quality of life will also be assessed using the validated Colostomy Impact Score questionnaire [13].

Postoperative clinical outcomes, including hospital length-of-stay, readmission, re-operation, mesh-related complications, and wound morbidity, will be captured in the ACHQC registry and in REDCap®. Wound morbidity, including SSIs, SSOs, and SSOPIs, will be reported using standard definitions [17].

Postoperative visits at 30 days, 1 year, and 2 years postoperatively (our practice standard-of-care) will include a physical exam and collection of patient-reported outcomes. Patient-reported outcomes will be assessed using the standard postoperative ACHQC questionnaire, which includes the short-form PROMIS Pain Intensity Scale and HerQLes. Additional postoperative questionnaires will capture Colostomy Impact Scores and Decision Regret Scales, validated for measuring regret after health care decisions [16].

Parastomal hernia recurrence will be evaluated by physical exam, patient-reported outcomes (colostomy impact score), and radiography. Physical exam will identify a parastomal hernia if there is bulging in the vicinity of the stoma. Colostomy impact score will identify a recurrence if patients respond “Yes, I have a small bulge (under 10 cm)” or “Yes, I have a larger bulge (over 10 cm).” CT recurrence will be defined as protrusion of a separate and distinct segment of bowel or other intra-abdominal contents within the musculofascial aperture. Three surgeons, blinded to the operative surgeon and repair technique, will evaluate radiographic recurrences, and at least two of three assessors must agree on radiographic hernia recurrence for it to be documented as such.

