### Adverse event reporting and harms {22}

All adverse events are captured by the research coordinator and reported annually to the IRB and to the DSMB each time it meets. All serious adverse events (e.g., return to the operating room within 30 days or mesh-related complication) are reported to the DSMB immediately.

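### Re-operation and mesh-related complications can occur after 30 days, but {20a} gives them only a crude comparison of proportions and accounts for follow-up time only for recurrence (minor)

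*Protocol article*

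**What the plan says.** Protocol article, Statistical methods {20a}, secondary-endpoint paragraph: "Comparisons of categorical endpoints will be performed using chi-squared tests" or Fisher's exact test. No other method is named for yes/no secondary endpoints. The same paragraph spells out the reasons that make up re-operation, ending with "mucocutaneous stoma disruption, and hernia recurrence requiring reoperation".

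Outcomes {12} lists re-operation and mesh-related complications without a time window, beside a morbidity item that is limited to 30 days. Adverse event reporting {22} gives, as examples of serious events, "return to the operating room within 30 days or mesh-related complication"; the 30-day limit there belongs to the return to theatre and not to the mesh complication.

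The primary-endpoint paragraph of {20a} says "Unbalanced follow-up times will be accounted for by using rate ratio and rate difference" and adds a Cox model for time to recurrence as a sensitivity analysis. Neither provision is repeated for the secondary endpoints. Section {20c} excludes multiple imputation of follow-up measures and mentions pattern mixture models only as something to consider if missingness looks non-random.

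On capture, {18a} says that "re-operation, mesh-related complications, and wound morbidity, will be captured in the ACHQC registry" and in REDCap, and {22} says "All adverse events are captured by the research coordinator". On loss, Sample size {14} says "Assuming a 20% rate of patients lost to follow-up".

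**The concern.** Follow-up time is allowed for when recurrence is analysed, but not when reoperation for that recurrence is analysed, although both build up over the same 2 years. A two-by-two table has no proper cell for a patient last known to be event-free at, say, 8 months. Counting that patient as a non-event lowers the reported risk. Dropping patients who were lost without an event raises it, because those with an early event stay in.

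At stake are the absolute 2-year risks of two harm endpoints, which surgeons and patients will set against any gain in recurrence. The method is stated in the article, so this is more than a detail left to an analysis plan.

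**Working it through.** The plan gives no event rate for these endpoints, so there is no stated figure to reproduce. What follows is an illustration.

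**Inputs**
- 71 patients per arm: the enrolment goal of 142 in {14}, divided by 2.
- Loss L by 2 years: 20% is the {14} figure, which was set for recurrence; 5% and 10% are shown as assumptions because capture of these events may be better.
- True 2-year risk F of 20% or 10%: assumed.
- Constant hazards for event and loss: assumed.

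**Formulas**
- Event hazard h = −ln(1−F)/2; loss hazard d = −ln(1−L)/2.
- Lost patients counted as event-free: P = h/(h+d) × (1 − exp(−2(h+d))).
- Patients lost without an event dropped: P / (P + (1−F)(1−L)).

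**Worked case, F = 20%, L = 20%.** Here h = d = 0.1116, so P = 0.5 × (1 − 0.80 × 0.80) = 0.5 × 0.36 = 0.180. With the lost dropped: 0.180 / (0.180 + 0.64) = 0.220.

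| True risk | Loss | Lost counted event-free | Lost without event dropped |
|---|---|---|---|
| 20% | 5% | 19.5% | 20.4% |
| 20% | 10% | 19.0% | 20.9% |
| 20% | 20% | 18.0% | 22.0% |
| 10% | 20% | 9.0% | 11.1% |

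**Early events.** If half of the events occur at once (stoma necrosis and mucocutaneous disruption would tend to be early), the remaining conditional risk is 0.10/0.90 = 0.111. The crude risk at 20% loss is then 0.10 + 0.90 × 0.0998 = 19.0% instead of 18.0%.

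**Death as a competing event** (hazard equal to 5% over 2 years, F and L both 20%). The crude figure is 18.0% and the Aalen-Johansen estimate 20.0%, so the pattern is the same.

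**Between-arm test** (simulation of 10,000 trials, 71 per arm, lost patients counted event-free for chi-squared):
- Equal 20% loss, equal true risk of 20%: type I error 5.0% for chi-squared, 4.9% for log-rank.
- Equal 20% loss, power at 10% vs 30%: 82.5% vs 83.2%. Power at 5% vs 15%: 47.7% vs 46.7%.
- Loss of 15% vs 25%, equal true risk of 20%: crude risks 18.5% vs 17.5%; type I error 5.3% vs 5.0%.
- Loss of 10% vs 30%, equal true risk of 20%: crude risks 19.0% vs 16.9%, a false gap of about 2 points; type I error 6.3% vs 5.2%.

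For scale, the 95% CI half-width for the difference at 20% risk is 1.96 × √(2 × 0.2 × 0.8 / 71) = 0.132, or about 13 points.

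**The case against.** The strongest reply is that the planned comparison works. With equal loss, chi-squared keeps its 5% error and has the same power as a time-to-event test. Distortion needs clearly unequal loss, which nothing in the article predicts: {17a} blinds participants, and {17b} foresees unblinding only after a complication that leads to re-operation, that is, after the event. This stands. A reader might infer that the test of these endpoints is invalid or that a harm difference would be manufactured; the documents do not support that.

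Second, the 20% loss belongs to an endpoint that needs examination, questionnaire and CT, whereas these events reach the registry, REDCap and the coordinator. This stands in part. Loss may be smaller, and at 5% to 10% the error is 0.4 to 1.0 point, against a one-arm standard error of √(0.2 × 0.8 / 71) = 4.7 points. But the article does not commit to complete capture in patients who stop attending, so zero loss cannot be assumed either.

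Third, no window is given, so the 2-year horizon is inferred. For re-operation the inference is firm, because reoperation for recurrence is named. For mesh-related complications it is weaker: {20a} mentions them only as a reason for re-operation, and they fall under the general rule for categorical endpoints through {12}.

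Fourth, denominators and censoring dates are usual matter for an analysis plan, and {20c} covers missing data in general. The first half is fair, and no fault is found with the absence of those details. The point rests on the one method that is stated and on follow-up handling that is written for recurrence alone. The conditional sentence in {20c} about pattern mixture models does not supply a method for partly observed follow-up.

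**Conclusion.** The point holds as a minor, cheap improvement. Section {20a} fixes a crude comparison for two endpoints that accrue beyond 30 days, and it accounts for follow-up time only for recurrence. If follow-up for these events is incomplete, the reported 2-year risk is off by up to about 2 points either way at a true 20% with 20% loss, and by 1 point or less at 5% to 10% loss.

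The size rests on assumed event rates, assumed loss and constant hazards, none of which the article gives for these endpoints. With complete capture to 2 years the crude proportion is correct. A reader might conclude that chi-squared must be replaced; the calculations show no gain in error control or power with equal loss, so changing the test is optional.

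**What to change.** Add to {20a}: for re-operation and mesh-related complications, report 2-year cumulative incidence by arm (Aalen-Johansen, death as a competing event) with the risk difference and 95% CI. Chi-squared or Fisher may stay as the test, and for the 30-day endpoints; Gray's test is optional.

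State the censoring date: the date to which event status is actually known (last registry, chart or coordinator contact), not the last attended visit. This matters. In a simulation with visits at 30 days, 1 year and 2 years, a true 20% risk and 20% loss, last-visit censoring gave 20.9% when events were captured up to loss and 22.8% when all events to 2 years were captured. Censoring at the known-status date gave 19.9%.

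If the rate ratio planned for recurrence is extended to these endpoints instead, test it with a score or exact test. A Wald test on the log rate ratio had 36.4% power at 5% vs 15%, against 47.7% for chi-squared.

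Cost: one or two sentences and a little more analysis work, with no added visits or patients. It needs an event date and a last-known-status date for each patient; the article does not say that the latter is recorded. The method assumes non-informative censoring and does not cure loss that is related to outcome.

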There are two standard mesh configurations to accommodate the stoma in an open retromuscular approach: keyhole and Sugarbaker. In the keyhole technique, the stoma is pulled through aligned apertures in the mesh and abdominal wall. Using this approach, parastomal hernia recurrence rates at a single institution were 11% at 13 months [8]. In the Sugarbaker technique, the apertures in the abdominal wall are offset and the bowel is placed over the mesh in the retromuscular space [10]. Recently, Pauli et al. found the parastomal hernia recurrence rate to be 4.5% at 10 months using the retromuscular Sugarbaker technique [11]. Additionally, a post hoc analysis of a large randomized controlled trial (RCT) comparing biologic versus synthetic mesh showed a parastomal hernia recurrence rate of 10% at 2 years for the Sugarbaker approach versus 30% for the keyhole approach in 108 patients (*p* = 0.07) (unpublished data). These promising results have prompted the urgent need to perform a well-designed RCT evaluating the outcomes of the two most common parastomal hernia repair approaches at our high-volume center.

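### Three patient-reported scores are collected before surgery, but the stated two-sample tests name no baseline adjustment, which gives up precision on secondary endpoints

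*Protocol article*

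**What the plan says.** Under Plans for assessment and collection of outcomes {18a}, the protocol article states that "Patient-reported quality of life at baseline will be collected with the standard ACHQC questionnaire", and names PROMIS Pain Intensity and HerQLes as parts of that questionnaire. It adds: "Preoperative stoma-related quality of life will also be assessed using the validated Colostomy Impact Score questionnaire". Under Outcomes {12}, the same three instruments, together with the Decision Regret Scale, are secondary endpoints at 30 days, 1 year and 2 years.

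Statistical methods {20a} gives one rule for every continuous secondary endpoint: "Comparisons of continuous endpoints will be performed using two-sample" t-tests, with the Wilcoxon rank-sum test as the alternative. It names no baseline term, change score or repeated-measures model for the patient-reported scores. The adjusted analyses in that section, a logistic and a Cox model, are for recurrence. Of the logistic model it says: "The adjusted model will include pre-specified covariates related to baseline disease severity". Those covariates are BMI, recurrent parastomal hernia, stoma disposition and stoma type. None is a patient-reported score.

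The missing-data section {20c} expects data to be missing at random, limits multiple imputation to baseline values, and excludes it for follow-up measures.

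**The concern.** For these three scores the patient's own preoperative value is a natural predictor of the later value. A two-sample test on the follow-up score leaves the variation that baseline explains in the error term, so the interval is wider than the collected data allow. It also leaves a chance difference between the arms at baseline partly uncorrected. The plan accepts covariate adjustment for recurrence but does not extend it to the outcomes that have a directly matching baseline measurement.

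A test at a single visit also uses only patients with a score at that visit. Because follow-up values are not imputed, a patient seen at baseline, 30 days and 1 year contributes nothing to the 2-year comparison.

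At stake is how much the trial can say about pain, hernia-related quality of life and stoma-related quality of life. The sample size was set for recurrence alone.

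**Working it through.** **Inputs.** The 5% level comes from {20a} ("Tests will be considered significant at a 5% level"); I take it as two-sided, which the article does not state. The number per arm comes from Sample size {14}: "power of 80%, we calculated a necessary sample size of 118 patients", that is, 59 per arm. The rates behind it are in Background {6a}: "parastomal hernia recurrence rate of 10% at 2 years for the Sugarbaker approach versus 30% for the keyhole approach in 108 patients". The baseline-to-follow-up correlation r is not in the documents, so I assume 0.3, 0.5 and 0.6. Baseline and follow-up standard deviations (SD) are taken as equal, and results are in SD units.

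**The plan's own figure.** With 0.30 versus 0.10 and unpooled variance, n per arm = (1.960 + 0.842)² × (0.30×0.70 + 0.10×0.90) / 0.20² = 58.87, rounded up to 59, or 118 in total. The stated size is reproduced. No size or power is stated for the patient-reported scores.

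**Precision.** The standard error of the unadjusted difference is √(2/59) = 0.184 SD, and the difference detectable with 80% power is 2.802 × 0.184 = 0.516 SD. ANCOVA multiplies the variance by 1 − r² and the detectable difference by √(1 − r²). The equivalent gain in patients is 1/(1 − r²) − 1. A test on change from baseline has relative variance 2(1 − r). The 0.5 SD difference used for power is illustrative only.

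| r (assumed) | ANCOVA variance, t-test = 1 | Equivalent extra patients | Detectable difference (SD) | Power for 0.5 SD | Change-score variance |
|---|---|---|---|---|---|
| no adjustment | 1 | – | 0.516 | 77.5% | – |
| 0.3 | 0.91 | 10% | 0.492 | 81.2% | 1.40 |
| 0.5 | 0.75 | 33% | 0.447 | 88.0% | 1.00 |
| 0.6 | 0.64 | 56% | 0.413 | 92.4% | 0.80 |

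The enrolment goal less 20% loss is 142 × 0.8 = 113.6, or about 57 per arm. The unadjusted detectable difference is then 0.525 SD and the variance ratios are unchanged.

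**Change scores.** The ratio of ANCOVA to change-score variance is (1 − r²)/[2(1 − r)] = (1 + r)/2, which is at most 1. A change-score test is therefore never more precise than ANCOVA, and for r below 0.5 it is less precise than the follow-up score alone.

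**Chance imbalance.** The baseline difference between arms also has standard error 0.184 SD, so its 95% range is about ±0.36 SD. The unadjusted estimate shifts by r times the imbalance. At the edge of the range this is 0.3, 0.5 or 0.6 × 0.361 = 0.11, 0.18 or 0.22 SD. Given that imbalance and no treatment effect, the test statistic has mean 1.96r and SD √(1 − r²). The chance of crossing ±1.96 is then about 8% (r = 0.3) and 13% (r = 0.5). For r = 0.6 the mean is 1.176 and the SD 0.8, so it is 1 − Φ(0.98), about 16%. With an imbalance of one standard error it is 5.0% at r = 0.3 and 4.8% at r = 0.5.

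**The case against.** The strongest reply is that nothing here is invalid. Randomization makes the unadjusted comparison unbiased, and over all randomizations the test keeps its 5% level. A reader might infer from the 8% to 16% above that type I error is inflated. It is not: those figures hold only given an extreme baseline imbalance. Nor does a chance imbalance pass in full into the estimate; only r times it does. Both corrections stand.

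Second, the sentence on continuous endpoints is generic, and the article does not say whether the tested quantity is the follow-up score or the change from it. One cannot assert that baseline is certainly ignored. That stands too, but it does not remove the point, because ANCOVA is at least as precise as either. Nor is the analysis simply left to an unseen plan: the article names the test.

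Third, a reader might lean on the Discussion, which suggests that patient satisfaction may matter more than recurrence. The Discussion ties that remark to the decision regret scale. Regret has no baseline and would stay with a two-sample test, so the remark lends no weight here.

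Fourth, the 1 − r² formula compares ANCOVA with the t-test, not with the rank-sum test that the plan also allows, and at r = 0.3 the gain is modest. Both are fair limits. The absence of a power calculation for secondary endpoints is ordinary and no defect.

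**Conclusion.** The point holds as one of efficiency, for PROMIS Pain Intensity, HerQLes and the Colostomy Impact Score. The plan pays for baseline measurements and names an analysis that, on its plain reading, does not use them. For an assumed r of 0.3 to 0.6, adjustment would cut the variance by 9% to 36%, which corresponds to 10% to 56% more patients. It would also remove the part of any realised baseline imbalance that carries into the estimate.

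The size rests on r, which the documents do not give, on equal baseline and follow-up variances, and on the t-test rather than the rank-sum test being used. The endpoints are secondary, and the conclusion on recurrence is unaffected. The change should be made, but it corrects no error of validity.

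**What to change.** In Statistical methods {20a}, state that these three scores will be analysed with the preoperative score as a covariate. The preferred form is a likelihood-based repeated-measures model over the 30-day, 1-year and 2-year visits, with arm, visit, arm-by-visit interaction and baseline score. Under the missing-at-random assumption already made in {20c}, it also uses patients with some visits missing. ANCOVA at each visit is simpler and gains the same kind of precision, but does not recover patients missing at that visit.

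Report the adjusted mean difference with its 95% confidence interval at each visit. Add a rank-sum test as a sensitivity analysis if the scores are markedly non-normal. Keep the two-sample tests for outcomes with no baseline value: length of stay, decision regret and 30-day opioid consumption.

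The cost is a sentence or two of analysis wording. The baseline scores are already being collected, and {20c} already provides for imputing those that are missing. No new patients, visits or questionnaires are needed.
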